### Outcome variables

#### Feasibility questions

Are eligibility criteria too inclusive or restrictive to recruit potential participants?How many participants do we need to assess to recruit eligible 30 participants?Are study groups balanced in numbers and demographics after simple randomization?How well subjects can incorporate the SBTs protocol with movement control exercises during clinic visits?How useful diary is in collection of detail of adherence for exercises, medication, usage of other therapies, and possible adverse events during exercise?What is the dropout rate in this study setting?

The main feasibility criteria progress information for potential full-scale trial are introduced on Table 1.

**Table 1 Tab1:** The main feasibility progression criteria

Feasibility criteria	Interpretation	Progress information to potential full-scale trial
Specific breathing protocol	Add-on breathing technique	Acceptable participants adherence of breathing protocol during clinic visits
Outcome measures	Diary data	Acceptable participants adherence of home exercises
	Patient-reported outcome measures	Clinically relevant outcomes measure differences between groups
	Patient-reported outcome measures	Clinically relevant outcome measures responsiveness in order to choose primary and secondary outcome measures for larger scale study
Eligibility criteria	Inclusive or restrictive recruitment criteria	Successful recruitment in acceptable time frame
Randomization	Simple randomization	Balance study groups in numbers and demographics

#### Outcome measures

Outcome measures are assessed on the baseline and at the two-month follow-up only in aim to avoid wasting resources if there are no relevant group differences in outcome measures. Multiple CLBP-related PROMs are included to help determine responsiveness of outcome measures and whether progression to a full-scale trial is worthwhile.Numerical pain rating scale (NRPS). The NRPS is a widely used subjective assessment of pain. It is an 11-point numerical pain scale ranging from 0 (no pain) to 10 (worst imaginable) [53]. More than 1.5-point change represent minimal detectable change (MDC) [54] and a 2-point change on the NPRS represents minimal clinically important difference (MCID) in participants with low back pain [47].The Roland-Morris Disability Questionnaire is a 24-item questionnaire used to evaluate CLBP-related disability. The scale ranges from 0 (no disability) to 24 (maximum low back pain-related disability) [55, 56]. The MCID difference is estimated to be a change of 2 to 3 points compared to the baseline score for low back pain patients [57].The Central Sensitization Inventory (CSI) was developed as a tool for screening central sensitisation (CS) [58]. It is a two-part questionnaire in which part A contains 25 questions on CS-related symptomology using a Likert scale from 0 = never to 4 = always. The total score ranges from 0 to 100. Part B includes ‘No/Yes’ and ‘year diagnosed’ questions about previous diagnoses related to CS-related disorders. Part B of the CSI is to provide information and is not scored [59]. MDC varies from 5.9 to 8.9 between different low back pain populations [60]. The CSI has been translated into Finnish and validated among a Finnish CLBP population [61].The Generalized Anxiety Disorder Assessment (GAD-7). The GAD-7 is a self-reported measure of generalised anxiety disorder–related symptoms. The items are rated over the preceding two weeks from not at all = 0 to 3 = nearly every day. Thus, the total scale ranges from 0 (the most minimal anxiety) to 21 (the most severe anxiety) [62]. The MCID score for GAD-7 is 4 [63]. The GAD-7 has been adapted and validated in Finnish [64].The Tampa Scale of Kinesiophobia (TSK). The TSK is used for assessment of subjective kinesiophobia (fear of movement). It has 17 statements related to kinesiophobia, with answers ranging from ‘strongly disagree’ to ‘strongly agree’, yielding a total range from 17 (minimal kinesiophobia) to 68 (maximal kinesiophobia) [65]. The MDC score is 8 [66] and MCID score TSK is 5.5 [67] The TSK has been translated into and validated in Finnish [68].The Pain Catastrophizing Scale (PCS). The PCS is used to assess the tendency to magnify the threat value of a pain stimulus. Thirteen items are scored on a Likert scale from 0 to 5, producing total scores from 0 (no catastrophising thoughts) to 52 (maximum catastrophising thoughts) [69]. The MDC score is 8 [69]. The PCS has been translated into Finnish but has not been cross-culturally validated. This study is part of its cross-cultural validation in Finnish.The Pain Self-Efficacy Questionnaire (PSEQ) includes 10 items. It is developed to assess the self-efficacy that people in pain have in their daily activities. The scale ranges from 0 points (not at all confident) to 6 points (completely confident). The PSEQ is applicable to all chronic pain conditions, but has mostly been validated on CLBP populations with the MDC score is 11.5 and MCID score from 5.5 to 8.5 [70]. The PSEQ has been translated into and validated in the Finnish language [71].The Pain and Sleep Questionnaire Three-Item Index (PSQ-3). This is a three-question questionnaire studying the effects of pain on sleep. The scale ranges from 0 (pain does not affect sleep) to 30 (pain has maximum effect on sleep) [72]. The PSQ-3 has been translated into Finnish and validated among a Finnish CLBP population [73].The first part of the EuroQol (EQ-5D-5L) is used to assess five dimensions of health-related quality of life [74]—mobility, self-care, usual activities, pain/discomfort and anxiety/depression—on a Likert scale (0 = no problems, 1 = slight problems, 2 = moderate problems, 3 = severe problems, 4 = unable/extreme problems). The EQ visual analogue scale (EQ VAS) is the second part of the EQ-5D-5L [74]. As a standard value set has not yet been studied for the Finnish population, a value set from a Danish population was used to calculate the index value. This is recommended by the EuroQol EQ-5D-5L User Guide [75].The Well-Being in Pain Questionnaire is a self-developed 11-question questionnaire to screen for the effects of pain on a person's biopsychosocial well-being using a Likert scale from 0 = never to 4 = always. Total scores range from 0 (no subjective well-being in pain) to 44 (maximum subjective well-being in pain). The questionnaire is a novel measurement developed by the first author and collaborators. This study is part of its validation.

A home diary will be used to monitor the regularity and estimate the amount of time spent in minutes on home exercises every day for the eight-week study period. Moreover, the home diary will be used to collect the participants’ use of pain medication (frequency of use, type, dose), other treatments or co-interventions for the treatment of pain (e.g. massage, chiropractic, manual therapy, physiotherapy) and possible adverse events and injuries related to the movement control exercises at home. The daily home diary will be identical for both groups.

The movement control tests will be assessed again during the last fourth clinical appointment to compare test results to those prior to the study period.

#### Shared in-clinic treatment protocol for both groups

A single clinician (the first author) will administer the assessment and treatment of movement control exercises to both groups. The first author is an experienced and long-term clinician in treating chronic musculoskeletal pain with exercises and breathing exercises. The advantage of this single-clinician study design is its ability to minimise the intervention differences and effects of contextual factors, such as clinic environment, location, architecture, interior design and therapists’ behaviour, communication and attitudes, which are well established as having a major effect on therapeutic placebo and/or nocebo effects in clinical encounters [76, 77].

After allocation to groups, each subject will be asked to attend four one-to-one contact sessions (30 min per session) on an individual basis over eight weeks. The most commonly anticipated in-clinic research appointment frequency is one week after the first session (week 2/8 in the study), two weeks later (week 4/8 in the study) and two weeks after that (week 6/8 in the study).

For both groups in the research appointments, visual demonstration, verbal guidance and/or hands-on assistance will emphasise the importance of motor learning focused on precision of movement control according to individual subject impairments. The primary goal of movement control intervention is to retrain optimal movement control and coordination of the spine, pelvis, hips and limbs to avoid ongoing nociceptive input secondary to suboptimal tissue loading [8].

The movement control exercises are intended to treat flexion (nine different exercise candidates), extension (nine different exercise candidates) and/or lateral flexion–rotational movement impairments (five different exercise candidates), as shown in Table 2. Two out of 23 exercises (camel and cat exercises) are more stretching type of exercises, in which the movement control exercise aim is to learn to return to a neutral spine after stretching. The exercises are mainly adapted from previous studies and the movements control handbook for treating CLBP by Luomajoki [14, 78, 79].

**Table 2 Tab2:**
[figure not shown]
Movement control exercises

The exact exercises will be chosen according to the individual movement impairment, but similar exercises will be emphasized in both groups. Alternative exercises will mainly be used if an exercise is not applicable because of aggravation of pain or because it is physically too easy or challenging to perform. Hence, movement control exercise variation will be minimized by employing similar exercises in both study groups.

Progress in the precision of movement control will be assessed at each research appointment. There will be between three and six exercises provided in the first research appointment to treat major movement control impairment identified by low back movement control tests. Further exercises will be given according to individual needs with the expectation that there will be between 8 and 14 different exercises by the final fourth research appointment. In a situation in which there is no specific movement control impairment on any test, all exercises in the study can be applied according to the exercise protocol to ensure variation in exercises. The employed exercises, sets and repetitions will be documented in written home exercise sheets documented by the first author and a group comparison will be carried out between these in the final report.

The treatment protocol is minimalist. It is not intended to include pain neuroscience education, other therapeutic modalities or lifestyle advice. The aim is to avoid mixing treatments in order to evaluate more precisely the outcome differences of the study groups.

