## Methods

### Trial design

A parallel randomised analyst-blinded feasibility trial with two-month follow-up. The study will be carried out in a single private chiropractic clinic. The study is a single blinded as administer will not be blinded for study intervention.

Thirty participants after meeting eligibility criteria will be allocated to movement control exercises with SBTs (experimental group) or movement control exercises without SBTs (control group) with an allocation ratio of 1:1.

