#### Home exercise protocol

The treatment protocol of the study emphasises home exercise because in a previous study of the mechanism of yoga on the treatment of CLBP, the biggest mediator on decreased disability was increased self-efficacy [84]. The participants in both groups will be instructed to practice the prescribed exercises as many days as possible in a week. The maximum recommended daily time for exercise will be 20 min per day. Participants will be instructed to continue any other exercises they performed before the start of the study.

The general home instructions provided on the sheets are as follows:Maintain a neutral lumbar spine during the exercises.Synchronise your breathing with the movements (Note: The breathing instructions are only included on the exercise sheets for group 2).Have breaks between sets and exercises according to your individual needs.Try to practice your exercises regularly/once a day.Remember to regularly update your home diary.

The home exercise sheets are accompanied by individually prescribed repetitions and sets of each exercise from the first author. The participants will have been given the possibility of contacting the first author via email or phone for further clarification of any exercise-related matter. All exercises used in the study with original written home instructions translated from Finnish with breathing instructions are included ins Appendices 1, 2 and 3. The breathing instructions comprise the only difference between the home exercise sheets; they are only provided to group 2.

The protocol of the study attempts to promote identical clinical encounters and treatments for both groups with only the difference of the SBTs add-on for group 2. Different aspects of these efforts are summarised in Table 3.

**Table 3 Tab3:** Summary of efforts to promote practically identical clinical practice exercise programmes

Clinical entity	Aim
Inclusion and exclusion criteria	Include only subjects who are adults with low back pain lasting more than three months (pain sensation more than three days per week) to promote a uniform pain population
	Exclude known cardiovascular, respiratory, rheumatic and neurological diseases potentially affecting breathing mechanics and hence potentially affecting the effects of SBTs

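### An unblinded clinician sets each participant's exercises, sets and repetitions after allocation, so the identical-programme contrast rests partly on discretion; the first prescription could be fixed beforehand at small cost

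*Protocol article*

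**What the plan says.** All references are to the protocol article.

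- **Aim of the design.** Home exercise protocol: the trial attempts to "promote identical clinical encounters and treatments for both groups with only the difference of the SBTs add-on". The same section says that the breathing lines are all that distinguishes the two groups' home sheets.
- **Who prescribes.** Trial design: "The study is a single blinded as administer will not be blinded for study intervention". Shared in-clinic treatment protocol for both groups: one clinician "will administer the assessment and treatment of movement control exercises to both groups".
- **When.** Same section: "After allocation to groups, each subject will be asked to attend four one-to-one contact sessions".
- **What is chosen.** There are 23 candidate exercises. Below Table 2: "The exact exercises will be chosen according to the individual movement impairment, but similar exercises will be emphasized in both groups", and "There will be between three and six exercises provided in the first research appointment". More are added by individual need, to an expected 8 to 14 by the fourth visit. Home exercise protocol: the same clinician sets repetitions and sets for each person.
- **What is known beforehand.** Recruitment: the movement control tests are done at the eligibility visit, before the first research appointment.
- **Who makes the list.** Randomization procedure: the same clinician generates it in SPSS before recruitment, and participants enter in the order in which they qualify.
- **Safeguards.** Table 3 aims for a similar number of exercises at each visit. The Home exercise protocol sets one daily time maximum of 20 minutes for both groups. The text below Table 2 plans to record exercises, sets and repetitions and compare them between groups. Strengths and limitations concedes that delivery by one clinician affects objectivity and that the therapist is not blinded.

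**The concern.** In most exercise trials an unblinded therapist is an unavoidable and accepted limitation. Here the exercise content has to be equal in the two arms for the contrast to mean what the title says. Knowing the arm while delivering treatment cannot be avoided. Knowing the arm while deciding what to prescribe can be avoided, at least for the first sheet.

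No deliberate bias is needed. Sessions last 30 minutes in both arms, and group 2 must also learn to match a breathing cycle to each movement. That could lead the clinician towards a different number, choice or volume of exercises in that group. The article does not say that this will happen, but its procedures leave room for it. A difference in patient-reported outcomes would then reflect exercise content as well as breathing. Table 1 makes clinically relevant between-group differences in those outcomes one of the progression criteria, so such a difference would feed into the decision on a full-scale trial.

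**Working it through.** **1. The plan's own figures.** The article makes no sample-size calculation, so there is none to reproduce. Its counts agree: 9 flexion + 9 extension + 5 lateral flexion-rotation = 23 exercises, and 15 + 15 = 30 participants.

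**2. Order of events, from the sections cited above.**

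1. The treating clinician generates the allocation list, before recruitment.
2. Eligibility visit: movement control tests done and recorded.
3. Questionnaires completed at home; the participant qualifies and takes the next place in order.
4. First research appointment, after allocation: 3 to 6 exercises chosen, with sets and repetitions.
5. Visits 2 to 4: further exercises, to an expected 8 to 14.

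The information that guides step 4 exists at step 2, so the first sheet can be written between steps 3 and 4. Because of step 1, earlier writing alone does not blind the writer. Whoever made the list could know the next assignment.

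**3. What the planned comparison of sheets can show.** The article gives no alpha and no SD for prescribed content. I assume a two-sided 5% level, equal SDs and 15 per arm, and express differences in SD units.

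- Half-width of the 95% CI = t(0.975; 28) × √(2/15) = 2.048 × 0.365 = 0.75 SD.
- Power from the noncentral t with 28 degrees of freedom and noncentrality d × √(15/2):
  - d = 0.5: about 26% (normal approximation 28%).
  - d = 0.8: about 56% (normal approximation 59%).
- Difference detectable with 80% power: about 1.06 SD (normal approximation 1.02 SD).
- If only 12 per arm had usable sheets (my assumption), the half-width would be 2.074 × √(2/12) = 0.85 SD.

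A comparison that finds no difference is therefore compatible with a true difference of up to about three quarters of an SD in either direction.

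**4. Share of the programme that an early first sheet would cover.** Share = first-visit count / final count.

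| Pairing | Share | Exercises still added later |
|---|---|---|
| Low with low | 3/8 = 38% | 5 |
| High with high | 6/14 = 43% | 8 |
| Smallest possible | 3/14 = 21% | 11 |
| Largest possible | 6/8 = 75% | 2 |

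These are shares of the exercise count, not of sets, repetitions or minutes.

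**The case against.** **The safeguards are more than a statement of intent.** Table 3 aims for a similar number of exercises per visit, which bears directly on the worry about fewer exercises in one arm. There is one daily time maximum, the candidates are grouped by direction of impairment, and alternatives are mainly for stated reasons. This stands, and it narrows the room for a difference. It does not settle which exercises are given, or how many sets and repetitions.

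**A reader might infer a two-fold (6/3) or 1.75-fold (14/8) difference between arms.** The article does not support that. The ranges describe individual participants. An arm difference of that size would need everyone in one arm at the minimum and everyone in the other at the maximum, against the similar-number aim.

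**A reader might infer that reordering one step removes the discretion at no cost.** It does not, because the clinician generates the list. Someone else has to hold it, which is a small but real cost.

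**The issue is recorded and admitted.** The sheets will be compared and the single-clinician limitation is stated. This stands, and reporting by arm is largely planned already. The additions are fixing the first sheet before the arm is known and recording the reasons for change.

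**The mechanism is not demonstrated.** This also stands. Breathing instructions are said to exist for every exercise, so none is excluded from group 2. The point is that the procedures permit a difference, not that one is expected.

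**Unseen material.** Table 2 is a figure not shown, and Appendices 1 to 3 are not available. A fuller rule linking tests to exercises cannot be excluded. If one exists, the point shrinks accordingly.

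**It is a 30-person feasibility trial with descriptive analysis.** True, but between-group outcome differences are a progression criterion, so a cleaner contrast still matters.

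**Conclusion.** The point holds as a modest, inexpensive improvement. On the text shown, equality of exercise content depends partly on the choices of one unblinded clinician, made after allocation. The planned safeguards limit or describe a difference but do not prevent one. The comparison of sheets cannot demonstrate identical programmes: its 95% CI half-width is about 0.75 SD with 15 per arm, under the assumed 5% level and equal SDs.

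The documents do not show that the arms will differ in content, or by how much. The improvement reaches only the first prescription, about 38% to 43% of the final exercise count with like paired with like. The conclusion assumes that the unseen table and appendices contain no binding selection rule.

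**What to change.** 1. Have an existing team member other than the treating clinician generate and hold the allocation list.
2. Once a participant qualifies, have the clinician write and date the first-visit sheet (exercises, sets, repetitions) from the recorded eligibility tests before the assignment is opened. Then add only the breathing lines for group 2. Sheets are needed for the 30 who qualify, not for all 120 expected to be assessed.
3. Log each later change with its reason, using those the protocol already names (pain aggravated, too easy, too demanding), and report changes by arm next to the planned comparison of sheets.
4. Reconcile the Home exercise protocol's statement that breathing lines are all that separates the sheets with its individual setting of sets and repetitions. Limit any claim of identical programmes to what the records show.

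Which exercises or volumes to prescribe is a clinical matter and is not addressed here.

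**Cost.** One small logistic step for holding the list, one change in the order of work and one extra column in the record. No added visit, test or participant is needed. Additions at visits 2 to 4, and later changes to sets and repetitions, remain unblinded.

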#### In-clinic SBTs add-on protocol for the experimental group (group 2.)

The SBTs used in the movement control exercises will follow the principles of the main therapeutic yoga styles [80–82] and breathing exercises that are the most commonly used in a healthcare setting [83]. The main practical aim of a specific breathing protocol is to keep it as simple as possible so that it can be more easily adapted by other therapists to other exercise treatment protocols in the future.Breathing through the nose if it feels easy and naturalMental focus on using abdominal breathingSynchronization of the breathing cycle (inhale-small pause-exhale-small pause) with movement during the movement control exercises. Detailed instructions for synchronization of the breathing cycle with the movement for each exercise are provided in detail in Appendices 1, 2 and 3.

In exercises, the synchronization of the breathing cycle with movements will mainly be based on different yoga styles that incorporate the Vinyasa method, which means synchronising breathing with movement, as in this study protocol [81]. Synchronisation of the breathing cycle with movement follows the simple general spine movement rule, whereby spine movement while *exhaling* involves bending forward and relaxing the spine and while *inhaling* involves expanse, straightening the spine and/or bending backwards [81, 82]. In several movement control exercises in the protocol, there are only upper and/or lower extremity movements, with static spine movement (e.g. weight shifts on one leg standing to the other) and for these, breathing synchronization varies according to the individual movement. Also, in different yoga styles, the exact instructions for synchronisation of breathing with movement vary for different movements. This study’s version of detailed synchronisation of breathing with movement for each exercise is described in detail in Appendices 1, 2 and 3.

